## Abstract

**Background:**

Adaptive interpersonal emotion regulation (iER) is a vital tool for positive relations. During early adolescence, peer relations become increasingly important, making this age group a relevant target group for interventions promoting positive interactions with each other, yet no evidence-based intervention exists for iER and early adolescents specifically.

**Methods:**

This randomised controlled trial (RCT) aims to test effectiveness and feasibility of a serious game training iER skills in early adolescents by comparing outcomes with a control group playing a game without psychoeducational content in a pre- and post-test design. German- and English-speaking early adolescents (10–14 years) are eligible for participation. IER skills improvement as assessed by a vignette task is the primary outcome and will be analysed with a chi-square test. Secondary outcomes include feasibility and acceptability, emotional competence, personal emotion regulation, gender, and sex.

**Discussion:**

This RCT will test whether playing a serious game about iER strategies results in an improvement of iER skills and whether the game is feasible and acceptable for early adolescents with the ultimate aim to implement the game in schools and help early adolescents achieve positive peer relationships.

**Trial registration:**

ClinicalTrials.govNCT04808102, Registered on 19 March 2021

## Administrative information

Note: the numbers in curly brackets in this protocol refer to SPIRIT checklist item numbers. The order of the items has been modified to group similar items (see http://www.equator-network.org/reporting-guidelines/spirit-2013-statement-defining-standard-protocol-items-for-clinical-trials/).

## Introduction

### Background and rationale {6a}

#### Interpersonal emotion regulation

Since the development of the process model of emotion regulation (ER) [1], numerous studies have investigated the ways and effects of ER [2, 3]. In the last decades, the concept of interpersonal ER (iER) has developed out of the concept of ER, but even though research about iER is on the rise, it has still received substantially less attention. In general, iER can be defined as deliberately influencing the emotions of another person [4]. Niven, Totterdell [4] found that iER can either improve or worsen affect. Improving others’ emotions can be achieved in two main ways: either dealing with the situation/emotion directly (positive engagement) or by focusing on the person experiencing the emotion without engaging with the emotion directly (acceptance, see Table 1). This classification has been validated by López-Pérez, Morillo [5] and will therefore be used in this protocol and study.

**Table 1 Tab1:** Classification of adaptive iER by Niven, Totterdell [4]

Cluster	Positive engagement		Acceptance	
Sub-cluster	Affective engagement	Cognitive engagement	Humour	Attention
Definition	Improve way the target feels about a situation	Change way the target thinks about a situation	Be humorous to communicate validation	Give the target attention to communicate validation
Example	Listen to the target’s problems	Give the target advice	Joke with the target	Make clear you care about the target

Henceforth, we will use the terms “personal ER (pER)” for regulating one’s own emotions and “interpersonal ER (iER)” for regulating someone else’s emotions to clearly distinguish between the two concepts.

#### Sex differences in iER

Sex differences have been found in pER [6, 7], but data is lacking when it comes to iER specifically. In the general population, females seem to have better interpersonal skills than males, while males score higher on intrapersonal skills [8] and studies about related concepts such as emotional intelligence [9], emotional reliance [10], or coping [11] found sex differences.

To our knowledge, López-Pérez, Morillo [5] are the only ones who tested sex differences concerning specific iER strategies defined by classifications. They found that women tend to use positive engagement more often than men, which gives preliminary evidence that women engage in the social affective component of iER strategies more than men. In their study, age varied from 18 to 76, thus excluding the targeted group of our study. There might be stronger differences during adolescence when sexuality, and therefore also gender, starts to be an important topic [12].

#### Early adolescents and iER

One age group that might especially benefit from high iER skills are early adolescents (broadly defined as 10–14 years, see [13]). Due to rapid developmental and psychosocial advances [14], the relationship with peers becomes increasingly important during that time. They not only influence externalising behaviour such as alcohol and drug use [15] or risk behaviour [16] and academic achievement [17], poor peer relations are also related to social anxiety and depression [18]. Consequently, positive peer relations are a vital buffer for coping with stressors and maintaining good mental health during early adolescence.

IER is an important skill for successful communication and interaction. This includes, for example, communication skills, which are important for the perceived quality of a friendship [19]. Using iER strategies can improve feelings of trust and friendship with peers [20] and helps finding new friends [21].

Despite the importance of interpersonal relationships during early adolescence, existing studies mostly concentrate on pER. Findings from that domain suggest that pER has an influence on disordered eating [22], sexual behaviour [23], or mental health symptoms like depression [24].

#### Serious games

It has been shown that analogue intervention and prevention programs in general have the potential to improve social emotional skills and wellbeing [25], but furthermore, both research and industry have started to pay attention to the advantages of the digital settings of serious games [26] as a means of intervention and learning. Serious games can be broadly defined as games that have an aim surpassing simple entertainment [27].

In a meta-analysis, Wouters, van Nimwegen [28] found that teaching cognitive skills through serious games was more effective than conventional methods. A literature review by Hamari, Koivisto [29] and a meta-analysis by Sitzmann [30] also found that gamification can work. Yet, findings of positive effects are still weak due to meagre literature [31], underlining the need for rigorous testing of serious games. One important advantage of serious games is that they boost players’ motivation [29]. As gaming is a rapidly growing industry that adolescents deem highly entertaining and important [32], serious gaming can be a potent tool to engage early adolescents in a fun way to learn about social skills.

Most existing serious games on ER have a focus on pER [33, 34], but some have also included interpersonal components. For example, in SPARX [35], depressed adolescents learn both personal and interpersonal strategies (such as communication and negotiation skills), but to our knowledge, only one game has specifically focused on iER. López-Pérez and Pacella [36] examined iER in children (8–10 years) with the use of a serious game called Emodiscovery [37]. This game lets children use different adaptive and maladaptive strategies to handle various scenarios where someone needs to be cheered up.

### Limitations and rationale

Overall, there are some gaps and limitations in the existing literature that lead to the idea and necessity of this study, most importantly the lesser focus of research on iER and the lack of serious games for a general population of early adolescents.

Concluding, iER skills can influence the successful establishment and maintenance of friendships and relationships of early adolescents, yet literature on iER in that age group is scarce. Research thus far has not sufficiently understood the concept of iER and the potential of training it targeting adolescents on a broad scale in the general public. We aim to fill this gap by developing a serious game that helps early adolescents express their strategies in situations requiring iER skills. The development of the game included an extensive literature search on iER, and in-game strategy-options were generated by using original material from Niven, Totterdell [4] study, which the authors kindly provided. Co-development workshops with children of the relevant age group helped with including ideas and remarks from the target group. The interdisciplinary research team included a diverse range of professions such as psychologists, computer scientists, and playwrights.

### Objectives {7}

In this RCT, we will assess the impact of the web-based serious game on iER skills in early adolescents. The primary objective of this study is to compare the improvement in pre- and post-intervention knowledge about iER strategies between a group that plays the intervention/serious game and a control group that plays a game without psychoeducational content. The secondary objectives are to examine sex differences in the use of specific strategies and to evaluate feasibility and acceptability of the intervention. We will examine the effects on outcomes of the following potential confounding variables: gender, prior gaming experience, language, and pER.

### Research questions

*Effectiveness*: How effective is playing the iER adventure game (AG) compared to a control group in terms of skills and knowledge regarding emotions and iER?*Sex differences*: Do boys and girls prefer different specific iER strategies according to Niven et al. (2009)’s classification?*Feasibility*: Is the iER AG feasible and acceptable in the targeted population?

### Hypotheses

*Emotional skills*: Participants of the experimental group will be able to recall more adaptive iER strategies after playing the iER AG compared to the control group.*Emotional skills*: Participants of the experimental group will score higher on the Emotional Skills and Competence Questionnaire (ESCQ; Takšić et al., 2009) after the iER AG compared to baseline pre-test scores and compared to the control group.*Emotional skills*: Participants of the experimental group will score higher on the Emotion Regulation of Others and Self scale (EROS; Niven et al., 2011) after the iER AG compared to baseline pre-test scores and compared to the control group.*Sex differences*: In a computer animated game environment which requires players to use iER strategies in social interactions, male and female participants will prefer different iER strategies. Female participants are more likely to engage in positive engagement, whereas male participants are more likely to engage in acceptance.

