### Outcomes {12}

Our primary outcome in this study is the change of iER strategies participants can think of from pre (baseline)- to post-intervention, i.e. if the percentage of participants who improve their knowledge about possible iER strategies is higher in the experimental group compared to the control group. This is done via a vignette-task. The follow-up will be approximately 5 days after baseline measures.

In secondary analyses, we will test iER as a corroborating variable with a questionnaire. The questionnaire was not developed to measure change of iER skills over a short period of time (it asks for iER strategies use in the last 2 weeks) and is thus used as a complementary measure. As the game addresses general topics around emotions additionally to specific iER strategies, we will also examine the change in general emotional competence. Furthermore, effects of sex and gender on strategy choice and feasibility of the game will be examined.

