#### Secondary outcomes

*Emotion regulation skills*. The Emotion Regulation of Others and Self scale (EROS [42];) will be used to measure both personal and interpersonal ER. This scale includes four factors of ER: intrinsic (personal) affect-improving, intrinsic affect-worsening, extrinsic (interpersonal) affect-improving, and extrinsic affect-worsening and shows good internal reliability and construct validity. Of the overall 19 items, 9 measure extrinsic (interpersonal) ER and 6 extrinsic affect-improving ER. The instructions ask to report the extent the person had used the strategy over the past 4 weeks to try to change their own or someone else’s feeling on a five-point Likert scale (“not at all”, “just a little”, “moderate amount”, “quite a lot”, “a great deal”). One example item is: “I listened to someone’s problem.”. The mean score in an adult population for extrinsic affect-improving is 3.53, for extrinsic affect-worsening 1.20. Internal consistency ranges from *α* = 0.74 to *α* = 0.82. The measure will be translated into German according to standard recommendations for the translation and adaptations of questionnaires [43].

*Emotional competence*. To measure emotional competence in early adolescents, the Emotional Skills and Competence Questionnaire (ESCQ [44];) will be used. The questionnaire consists of 45 items on three subscales: the Perceive and Understand emotions scale (15 items; e.g. “When I see how someone feels, I usually know what has happened to him”), the Express and Label emotions scale (4 items; e.g. “I am able to express my emotions well.”), and the Manage and Regulate emotions scale (16 items; e. g. “When I am in a good mood, every problem seems soluble”). Ratings are given on a 5-point scale (“never” to “always”). Internal consistency ranged from α = .81 to .90 (Perception and Understanding), .78 to .88 (Express and Lable), and .67 to .78 (Manage and Regulate), and .88 to .92 (overall emotional competence). The measure will be translated into German by the same procedure as described before.

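### As written, a higher EROS score cannot be read as better interpersonal emotion regulation, and the scale's recall period is given as both 2 and 4 weeks

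*Protocol article*

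**What the plan says.** **Direction.** The Hypotheses section predicts that "Participants of the experimental group will score higher on the Emotion Regulation of Others and Self scale", both against their own baseline and against the control group. It names no subscale.

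**Instrument.** Under Secondary outcomes, the scale "will be used to measure both personal and interpersonal ER". Its four factors are "intrinsic (personal) affect-improving, intrinsic affect-worsening, extrinsic (interpersonal) affect-improving, and extrinsic affect-worsening". The item counts are: "Of the overall 19 items, 9 measure extrinsic (interpersonal) ER and 6 extrinsic affect-improving ER". Adult means are given for the two extrinsic factors only: 3.53 for improving and 1.20 for worsening.

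**Analysis.** Under Secondary analyses, each one-point change on an item scores +1 or −1 according to whether the answer gets better or worse, and groups are compared with a Wilcoxon test. No subscale, total score or reverse-keying is mentioned. Secondary p-values are to be read descriptively.

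**Recall period.** Outcomes {12} describes the questionnaire used to corroborate the primary outcome and says "it asks for iER strategies use in the last 2 weeks". Secondary outcomes says the instructions ask respondents to "report the extent the person had used the strategy over the past 4 weeks". Outcomes {12} does not name the scale, but EROS is the only questionnaire that the protocol describes as measuring interpersonal regulation.

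**ESCQ.** Secondary outcomes gives 45 items on three subscales of 15, 4 and 16 items (for the second: "the Express and Label emotions scale (4 items").

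**The concern.** The hypothesis puts one direction on an instrument whose factors do not share one. On the two affect-worsening factors, a higher score is not better skill. According to the Feedback section, the game blocks progress when maladaptive strategies are chosen, so success should push the extrinsic worsening items down. Taken literally, the hypothesis would count a rise on those items as support.

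More than half of the items concern the child's own emotions, a different construct from the one the primary vignette task measures. If all items are pooled, a true gain in improving others' feelings is spread over many items that need not move. If they are not pooled, the plan does not say which of four subscales carries the hypothesis, and the choice could be made after the data are seen.

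The recall conflict matters because the study is short. The longer the window, the more of what the child rates at post-test happened before the game was opened. The German version is still to be translated, so an unresolved period could reach the questionnaire and differ between languages.

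**Working it through.** **1. Item composition** (inputs: 19 items, 9 extrinsic, 6 extrinsic improving; Secondary outcomes)

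| Content | Items | Share |
|---|---|---|
| Extrinsic, improving | 6 | 6/19 = 32% |
| Extrinsic, worsening | 9 − 6 = 3 | 3/19 = 16% |
| Intrinsic, improving and worsening | 19 − 9 = 10 | 10/19 = 53% |

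The split of the 10 intrinsic items between improving and worsening is not given.

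**2. Dilution if all items are pooled** (pooling is an assumption; the plan does not fix it)

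Change in the 19-item mean = (6 × gain on target items + 3 × change on extrinsic worsening items) / 19, with intrinsic items unchanged.

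- Gain 0.50, worsening items unchanged: (6 × 0.50)/19 = 0.158.
- Gain 0.50, worsening items fall 0.50, not reverse-keyed: (3.0 − 1.5)/19 = 0.079. Reverse-keyed: (3.0 + 1.5)/19 = 0.237.
- Gain 0.25, worsening items fall 0.50, not reverse-keyed: (1.5 − 1.5)/19 = 0. Reverse-keyed: (1.5 + 1.5)/19 = 0.158.

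The loss of power depends on item variances and correlations, which the document does not give.

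**3. How far cancellation can go**

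The adult extrinsic worsening mean is 1.20. Item coding is not stated. If items run 1 to 5, the mean can fall by at most 1.20 − 1 = 0.20 per item, or 3 × 0.20 = 0.6 points in all. A gain of 0.6/6 = 0.10 on each target item offsets that. If items ran 0 to 4, the room would be 1.20 per item and the offsetting gain 3 × 1.20/6 = 0.60. On 1-to-5 coding, then, cancellation is small and dilution is the larger problem.

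**4. Recall window**

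Participant timeline {13} puts the pre-test on day 1 and the post-test on days 5 to 10, so 4 to 9 days elapse. Share of the window before baseline = (window − elapsed)/window.

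| Window | Post-test day 5 (4 days elapsed) | Post-test day 10 (9 days elapsed) |
|---|---|---|
| 2 weeks | (14 − 4)/14 = 71% | (14 − 9)/14 = 36% |
| 4 weeks | (28 − 4)/28 = 86% | (28 − 9)/28 = 68% |

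Counting 5 to 10 elapsed days instead gives 64% to 29% and 82% to 64%.

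**5. ESCQ**

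15 + 4 + 16 = 35, against 45 stated.

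**6. What is not touched**

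The plan gives no power figure for EROS. Its primary sample size of 62 per group (30% versus 10%, two-sided 0.05, 80% power) reproduces with the uncorrected pooled-variance formula (power 0.803) and does not depend on any of this.

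**The case against.** Several points on the other side are sound.

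- **EROS is not useless as corroboration.** A reader might infer that it cannot confirm the primary outcome at all. The document does not support that: it describes a separate 6-item extrinsic improving factor that could do so once named. Outcomes {12} speaks of interpersonal regulation as the corroborating variable, which points towards the extrinsic items.
- **No total-score test is specified.** The scoring rule can be read as direction-keyed, so that less affect-worsening counts as improvement. That reading removes the improving/worsening conflict. It departs from the plain prediction of a higher score, however, and still pools own with others' regulation.
- **The 10 intrinsic items are not simply off target.** One might add 10 and 3 and call 13 of 19 items misdirected. But the Abstract lists personal emotion regulation among the secondary outcomes, while Objectives {7} lists it as a potential confounder. The supportable statement is that these items measure something else and need separate reporting.
- **Weak sensitivity to short-term change is partly conceded.** Outcomes {12} says the questionnaire was not built for it and treats it as complementary. Both arms share the same window, so the effect is dilution, not bias towards one arm.
- **The stakes are limited.** EROS is secondary, its p-values are descriptive and the framework is exploratory.

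Scoring detail is often left to an analysis plan. What remains is not just missing detail: the published hypothesis states a direction that does not fit the published factor structure, and two sections give different recall periods.

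**Conclusion.** The point holds in limited form. As written, a higher EROS score is not interpretable as better interpersonal emotion regulation, because neither the hypothesis nor the analysis section fixes which subscale and which direction count as support. The main harm is an ambiguous direction and dilution: 6 of 19 items carry the target, so a 0.50-point gain on all of them moves a pooled mean by about 0.16 if the other items do not move. That figure assumes pooling, which the plan neither states nor excludes. Full cancellation of the gain by falling worsening scores is a tempting inference, but it is unlikely on the document's adult mean if items are coded 1 to 5.

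The recall period is a plain contradiction. It decides whether 36–71% (2 weeks) or 68–86% (4 weeks) of the rated window precedes baseline. This lowers sensitivity in both arms.

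The ESCQ mismatch (35 against 45) is minor and separate. A reader might take 45 as correct, but the document does not show whether the total or a subscale count is wrong.

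The primary outcome, its test and the sample size are unaffected.

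**What to change.** - Restate the EROS hypothesis with the 6-item extrinsic affect-improving subscale as the corroborating endpoint, expected to be higher in the experimental group.
- Report extrinsic affect-worsening separately, with the opposite expected direction.
- Report the two intrinsic subscales separately as personal-regulation outcomes, in line with the Abstract. Use their pre-test values where personal regulation is examined as a confounder under Objectives {7}.
- State in Secondary analyses that scores are formed and compared by subscale, and how items are keyed.
- Reconcile the 2-week and 4-week statements to one recall wording, used in both languages and at both time points.
- Reconcile the ESCQ total with its subscale counts against the instrument itself.

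The cost is the wording of one hypothesis, two measure descriptions, the recall statement in Outcomes {12} and a line in the analysis section. The protocol describes the trial as pre-recruitment with the German translation still to be done, so no data collection or sample size change is needed.

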### Trial design {8}

This trial is a RCT with an experimental and a control group, with participants being individually allocated to either of the groups. The allocation ratio is 50:50, and the framework is exploratory.

## Methods: participants, interventions, and outcomes

### Study setting {9}

This study will be conducted online and is consequently not linked to a specific country, but recruitment will take place primarily in German- and English-speaking countries with the main countries being Austria and the UK.

### Eligibility criteria {10}

Eligible participants will be early adolescents between 10 and 14 years. Furthermore, participants have to be able to read and understand German or English as the game can be played in these two languages. They must also provide written parental consent and be willing to participate in the study by filling out questionnaires at two time-points (pre- and post-test) and playing a web-based game in between. The game targets iER in the general population of early adolescents. Hence there will be no restrictions in terms of learning difficulties or mental health problems (see Table 2).

**Table 2 Tab2:** Eligibility criteria

	Inclusion criteria	
1.	Between 10 and 14 years old	
2.	Willing and able to provide written parental consent	
3.	Willing and able to participate in filling out pre- and post-test online questionnaires and playing a web-based game	
4.	Able to read and understand German or English	
5.	Access to a device with internet (computer, mobile phone, tablet)	

